#### 2.3.3 Safety outcomes

The safety outcomes will include the following items.

Incidence of adverse events and diseasesLiver function markers: changes in AST, ALT, and γ-glutamyl transpeptidase (γ-GTP)Glucose and metabolic markers: changes in hemoglobin A1c (HbA1c) and body mass index (BMI)Blood pressure and pulse: changes in systolic and diastolic blood pressure and pulse rateElectrolytes: changes in serum sodium and urinary sodium

#### 2.3.4 Exploratory outcomes

The exploratory outcomes will include the following items.

Changes in urinary levels of urate and indoxyl sulfateInflammation oxidative stress markets: changes in serum high sensitive C-reactive protein (hs-CRP) and in urinary 8-hydroxydeoxyguanosine (8-OHdG)Comparison between groups of patients who achieved and did not achieve serum urate levels of ≤6 mg/dL (baseline levels and changes)

Two analysis groups will be set for the efficacy of this study: Full analysis set (FAS) and per-protocol set (PPS), with FAS being the primary analysis. The FAS will be the population of eligible patients who have received the study drug and have serum urate readings at baseline and at least one time point during the observation period. The PPS will be the population from the FAS excluding the participants who deviated from the study protocol (e.g., use of concomitantly prohibited drugs or study drug adherence of <80%). The Safety Analysis Set (SAS) analysis population will be established for the safety of the study, and the SAS will be the population in which the study drug is administered and data on any of the safety outcomes are obtained.

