## 2 Methods and analysis

### 2.1 Design

The SWITCH SURI Study (efficacy and safety of SWITCHing from febuxostat to dotinurad, a novel Selective Urate Reabsorption Inhibitor, in hyperuricemic patients with type 2 diabetic kidney disease) is a single-center, single-arm, open-label, prospective trial. This is an exploratory study aimed at evaluating the effect of switching from febuxostat to dotinurad on the serum urate levels and renal impairment parameters, as well as the underlying factors and to evaluate the incidence of adverse events and changes in safety measures, such as liver enzymes, glucose, and metabolism (**Table 1**). This study will evaluate the rate of achievement of serum urate levels to ≤6 mg/dL at week 24 after switching to dotinurad.

**Table 1 T1:** Overview of All Visits and Tests Schedule.

Item	At informed consent	Observation period				At discontinuation
		Week 0	Week 4	Week 12	Week 24	
Permitted ranges of visits		0	±2 weeks	±4 weeks	±4 weeks	–
Informed consent	✓					
Demography	✓					
Study drug adherence			✓	✓	✓	✓
Concomitant therapy status		✓	✓	✓	✓	✓
Height, body weight		✓	✓	✓	✓	✓
Blood pressure, pulse rate		✓	✓	✓	✓	✓
Hematology tests		✓	✓	✓	✓	✓
Urinalysis		✓	✓	✓	✓	✓
Adverse events			✓	✓	✓	✓

Dotinurad will be started with Urece^®^ 0.5 mg tablet orally once daily within 1 week after the end of the baseline examination, and if the urate level remains above 6 mg/dL after ≥2 weeks, the dose of Urece^®^ tablets will be gradually increased (up to 4 mg), at observation points and at other scheduled visits, and continued until week 24 of the observation period.

Because of the potential to affect the evaluation of this study, the concomitant use of urate-lowering drugs (other than dotinurad), drugs that act on urate transporters (sodium-glucose cotransporter 2 [SGLT2] inhibitors, losartan, irbesartan), or drugs that affect indoxyl sulfate levels (spherical adsorptive carbon) is prohibited until the patient visit at 24 weeks after the start of dotinurad administration (except in case of discontinuation). However, in principle, drugs that patients already take before they provide consent may be continued from the date of consent until week 24, and the dosage and administration should be increased or decreased as appropriate according to medical conditions. Moreover, drugs deemed medically necessary may be added, except for the above prohibited concomitant medications.

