### 2.3 Outcome assessment

#### 2.3.1 Primary outcome

The primary outcome of this study will be the rate of achievement of serum urate levels of ≤6 mg/dL at week 24 of dotinurad treatment.

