### 2.5 Statistical analysis

Summary statistics of the background data of the study participants will be calculated. For nominal variables, the numbers in each category and their percentages will be shown; for continuous variables, the numbers, mean, standard deviation, minimum, median, and maximum values will be calculated.

The two-sided 95% confidence interval for the primary efficacy outcome of achieving a serum urate level of ≤6 mg/dL at week 24 of dotinurad treatment will be calculated, and a one-sample population proportion test will be performed for the null hypothesis of an achievement rate equal to 30%. Subgroup analysis will be performed by other candidate factors, such as subject background, to examine their impact on the primary outcome. For the secondary outcomes obtained from the metric data, summary statistics will be calculated at each observation point, a one-sample t-test or Wilcoxon’s signed rank test will be performed to evaluate their statistical significance, and if necessary, analysis of covariance and multivariate analysis will be performed. If the data are non-normally distributed, appropriate data transformations will be applied. When statistical tests are conducted, the significance level will be set at 0.05 two-sided, with the confidence coefficient for statistical estimation being 95% two-sided. Missing data in efficacy will be imputed using the last observation carried forward method.

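### Neither stated analysis set scores a patient as a dotinurad failure when a prohibited urate-lowering drug brings the week-24 urate to 6 mg/dL or below

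*Protocol article*

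**What the plan says.** Section 2.3.1 of the protocol article defines the primary outcome as "the rate of achievement of serum urate levels of ≤6 mg/dL at week 24 of dotinurad treatment". It sets no condition on what else the patient was taking.

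The analysis sets are described at the end of Section 2.3.4: "Full analysis set (FAS) and per-protocol set (PPS), with FAS being the primary analysis". Membership of the FAS requires "eligible patients who have received the study drug and have serum urate readings at baseline and at least one time point during the observation period", so use of a prohibited drug does not remove a patient. For the supporting set: "The PPS will be the population from the FAS excluding the participants who deviated from the study protocol (e.g., use of concomitantly prohibited drugs".

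Section 2.1 bans "the concomitant use of urate-lowering drugs (other than dotinurad), drugs that act on urate transporters" (SGLT2 inhibitors, losartan and irbesartan are named) and also spherical adsorptive carbon. The reason given is that they could affect the study's evaluation. The ban "is prohibited until the patient visit at 24 weeks after the start of dotinurad administration (except in case of discontinuation".

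Section 2.5 adds one rule for absent values: "Missing data in efficacy will be imputed using the last observation carried forward method". It covers missing data only. An observed week-24 reading taken on a prohibited drug is used as it stands. The primary test compares the achievement rate with 30%.

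**The concern.** The plan recognises that other urate-lowering drugs can distort the result, but its only stated response in the analysis is to exclude users from the PPS. Take a patient whose urate stays above 6 mg/dL on dotinurad, who is given another urate-lowering drug, and who then reads at or below 6 mg/dL at week 24. For the question of whether switching to dotinurad achieves the target, this patient is a failure. The FAS counts a success. The PPS takes the patient out of numerator and denominator.

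There is no control arm in which such use would also occur and partly cancel. The comparison is with a fixed number, so any conversion of a dotinurad failure into an achiever adds to the rate being tested. At n=50, each one adds 1/50 = 2 percentage points.

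**Working it through.** **Inputs.** Null rate 30%; success when the lower limit of the two-sided 95% interval exceeds 30%; 44 evaluable patients and a target of 50 (Sections 2.4 and 2.5). The type of interval is not named, so I use the exact (Clopper-Pearson) limit, in keeping with the binomial test cited in Section 2.4. The frequency of prohibited-drug use is not given and is treated as an assumption. The sample size of 44 plays no part in the argument beyond setting n.

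**Boundary.** With x achievers of n, the lower limit is L = Beta⁻¹(0.025; x, n−x+1).

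- n=50: 22/50 gives L = 29.99%; 23/50 gives 31.8%. Success needs at least 23.
- n=44: 19/44 gives L = 28.3%; 20/44 gives 30.4%. Success needs at least 20.

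**Effect of k patients at the boundary.** Suppose k of the observed achievers reached target only through a prohibited drug. The FAS as written gives x/n, failure scoring (x−k)/n, and the PPS (x−k)/(n−k).

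| n, k | FAS as written | PPS | Scored as failure |
|---|---|---|---|
| 50, 1 | 23/50 = 46.0%, L 31.8% | 22/49 = 44.9%, L 30.7% | 22/50 = 44.0%, L 29.99% |
| 50, 2 | 23/50 = 46.0%, L 31.8% | 21/48 = 43.8%, L 29.5% | 21/50 = 42.0%, L 28.2% |
| 44, 1 | 20/44 = 45.5%, L 30.4% | 19/43 = 44.2%, L 29.1% | 19/44 = 43.2%, L 28.3% |

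Two things follow.

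1. (x−k)/(n−k) is always larger than (x−k)/n, so for such patients the PPS rate lies above the failure-scored rate. The gap is 1.8 points at n=50, k=2.
2. Where the removed patients are achievers, the PPS rate lies below the FAS rate. The two sets both declare success in the first row and disagree in the other two.

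**Dependence on the interval.** The one-patient flip in the first row is specific to the exact limit, since 22/50 misses 30% by a hair. With the Wilson limit the boundary at n=50 is 22, and the same pattern occurs one patient lower.

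**Chance of a false success (illustration).** Let the true dotinurad-only rate be 30%, and let a share d of all patients become achievers only through a prohibited drug. The FAS then succeeds with probability P(X ≥ boundary), where X is binomial with rate 0.30 + d:

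| d | n=50 (≥23) | n=44 (≥20) |
|---|---|---|
| 0 | 1.2% | 2.2% |
| 2% | 2.7% | 4.3% |
| 4% | 5.3% | 7.6% |
| 6% | 9.4% | 12.6% |

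The nominal upper-tail error is 2.5%. It is passed at d of about 2%, which is one patient in 50.

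**The case against.** **The PPS is a working check.** A reader might infer that both sets err towards the drug, and so will agree and offer no check. The figures do not support that. Removing an achiever lowers the PPS rate relative to the FAS, and in two of the three boundary cases above the PPS misses success and so flags the problem. What stands is narrower: the PPS does not give the failure-scored rate, and the two sets can agree wrongly, as with one such patient at n=50.

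**Not every user is a dotinurad failure.** SGLT2 inhibitors, losartan and irbesartan may be started for reasons unrelated to urate, in patients already at target. Dropping such a patient lowers the PPS rate, so the direction of the PPS bias is not fixed across all prohibited drugs. This stands. It is why the primary rescoring below is confined to other urate-lowering drugs.

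**The situation is narrow.** The patient must stay in the study, breach an explicit ban, have been a failure on dotinurad, and be brought to target by the other drug. The plan already provides for dotinurad dose increases. It lifts the ban on discontinuation, and where a discontinued patient has no week-24 value the missing-data rule applies instead. This stands, and it limits the likely size.

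**An unseen document may settle it.** No sentence says outright that these patients count as achievers, and the full protocol or analysis plan could add a failure rule. But the article is not silent here. It states the outcome, both sets, which is primary, what happens to prohibited-drug users, and how missing values are treated. The point concerns what those stated rules produce together.

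**Conventional pairing, exploratory study.** Keeping observed values in the FAS with a PPS in support is common practice, and the trial calls itself exploratory. It nevertheless sets a formal test against 30%, and that test is what is exposed.

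**Conclusion.** The point holds in limited form. On the stated rules, an observed week-24 reading at target while taking a prohibited urate-lowering drug is an achievement in the primary FAS and is removed from the PPS, so neither analysis treats that patient as a dotinurad failure. The FAS rate can be biased upward against 30%. For users who would have failed on dotinurad, the PPS rate exceeds the failure-scored rate, though it may be below the FAS rate.

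The size depends on a frequency that the document does not give; with no such use there is no effect. A reader might take the 5.3% or 9.4% at n=50 as the trial's actual error rate. They are not: they assume a true rate of exactly 30% and that 4% or 6% of all patients are converted. What can be said firmly is that one patient can change the conclusion at the boundary.

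**What to change.** Add to the definition of the primary outcome: in the FAS, a patient who took a urate-lowering drug other than dotinurad between Week 0 and the week-24 reading is a non-achiever and stays in the denominator. State that febuxostat taken before the first dotinurad dose does not count, since Section 2.1 allows up to a week between the baseline examination and that dose.

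Report two sensitivity analyses:

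- (a) the observed reading regardless of prohibited drugs, which is the present FAS rule;
- (b) the same non-achiever scoring extended to SGLT2 inhibitors, losartan and irbesartan.

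The PPS can remain as a supporting set.

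The cost is one sentence and two extra proportions. Table 1 already records concomitant therapy at Week 0, at each later observation visit and at discontinuation, so no new data are needed. The change affects scoring only, not treatment. The downside is that the reported rate may be slightly lower, and that a patient already at target before taking such a drug would be scored conservatively. Analysis (a) shows how much that matters.

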### 2.4 Sample size calculation

The target sample size will be set at 50. To evaluate the efficacy of switching to dotinurad in the participants in the study, a threshold value of 30% was set based on the achievement rate of serum urate levels of ≤6 mg/dL (20%) with 40 mg of febuxostat. To demonstrate that the lower limit of the two-sided 95% confidence interval exceeds the threshold of 30%, a significance level of α = 0.05 (two-sided) and a power of 1-β 90%, the required sample size was calculated by a binomial probability hypothesis test, resulting in 44. Considering dropouts, the target sample size will be set at 50.

### 2.5 Statistical analysis

Summary statistics of the background data of the study participants will be calculated. For nominal variables, the numbers in each category and their percentages will be shown; for continuous variables, the numbers, mean, standard deviation, minimum, median, and maximum values will be calculated.

The two-sided 95% confidence interval for the primary efficacy outcome of achieving a serum urate level of ≤6 mg/dL at week 24 of dotinurad treatment will be calculated, and a one-sample population proportion test will be performed for the null hypothesis of an achievement rate equal to 30%. Subgroup analysis will be performed by other candidate factors, such as subject background, to examine their impact on the primary outcome. For the secondary outcomes obtained from the metric data, summary statistics will be calculated at each observation point, a one-sample t-test or Wilcoxon’s signed rank test will be performed to evaluate their statistical significance, and if necessary, analysis of covariance and multivariate analysis will be performed. If the data are non-normally distributed, appropriate data transformations will be applied. When statistical tests are conducted, the significance level will be set at 0.05 two-sided, with the confidence coefficient for statistical estimation being 95% two-sided. Missing data in efficacy will be imputed using the last observation carried forward method.

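### LOCF in an FAS that requires a post-baseline urate scores patients who stop early at target as week-24 successes; compared with counting them as not achieved, it can never lower the rate tested against 30%

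*Protocol article*

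**What the plan says.** - Outcome (section 2.3.1): "the rate of achievement of serum urate levels of ≤6 mg/dL at week 24 of dotinurad treatment".
- Analysis set (end of section 2.3.4): two efficacy sets are defined, "with FAS being the primary analysis". To enter the FAS, treated eligible patients must "have serum urate readings at baseline and at least one time point during the observation period".
- Missing data (section 2.5): "Missing data in efficacy will be imputed using the last observation carried forward method". The sentence covers all efficacy data and gives no separate rule for the primary outcome.
- Test (section 2.5): "a one-sample population proportion test will be performed for the null hypothesis of an achievement rate equal to 30" percent. Section 2.4 gives the aim: "To demonstrate that the lower limit of the two-sided 95% confidence interval exceeds the threshold of 30" percent.
- Dosing (section 2.1): dotinurad starts at 0.5 mg and is raised stepwise, to at most 4 mg, while urate stays above 6 mg/dL.
- Visits (Table 1): laboratory tests at weeks 0, 4, 12 and 24, and at discontinuation.

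**The concern.** The outcome asks whether a patient is at target at week 24 of dotinurad. Under LOCF, a patient who stops around week 4 or 12, for an adverse event or any other reason, and whose last reading was at target is scored as a success at week 24 of a treatment no longer being taken. The reading at the discontinuation visit may be the one carried forward, and it reflects drug that has only just been stopped. A treated patient with no reading after baseline disappears from both numerator and denominator.

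The study has one arm and a fixed threshold, so no control group is subject to the same rule. At stake is whether a lower confidence limit above 30% means that enough patients were at target on treatment at week 24, or only that enough were at target when last seen. The per-protocol set does not settle this: it is a subset of the FAS, and the same imputation rule applies to it.

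**Working it through.** **Inputs from the article.** Null rate 30%; success when the lower limit of the two-sided 95% interval exceeds 30% (upper tail 2.5%); required number 44; target 50. The step from 44 to 50 implies an allowance of 50 − 44 = 6 dropouts, or 6/50 = 12%. The article does not state this rate.

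**The plan's own figure.** Section 2.4 reports "the required sample size was calculated by a binomial probability hypothesis test, resulting in 44". It gives no expected rate, so 44 cannot be derived from the stated inputs alone. An exact binomial test against 30% first reaches 90% power at n = 44 if the expected rate is 54% or 55%. It then needs 20/44 (upper-tail probability under 30%: 2.18%), with power 92.2% at 55%. The figure is consistent with an exact rule, so exact (Clopper-Pearson) limits are used below. The missing expected rate is a separate matter and does not affect this point.

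**Passing rule at 50.** 22/50 has a lower limit of 29.99% and fails; 23/50 has 31.8% and passes.

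**Direction.** Let c be the completers at target, s the early stoppers last seen at target, and m the treated patients with no post-baseline urate.
- Missing as not achieved: c/50.
- LOCF in the FAS: (c + s)/(50 − m).

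Since s ≥ 0 and m ≥ 0, the second is never below the first. With 44 completers and 6 stoppers, any c from 17 to 22 fails under the first rule and can pass under the second, because 17 + 6 = 23. Example with c = 20 and s = 3: 20/50 = 40.0% (lower limit 26.4%, fails) against 23/50 = 46.0% (31.8%, passes).

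**Size when the true rate is 30% with dropouts as failures.** Take 44 completers and 6 dropouts, all 6 with a post-baseline reading. The completer rate is 0.30 × 50/44 = 34.1%. If a share q of dropouts is last seen at target, the expected LOCF rate is 0.30 + 0.12q. The chance of passing is P[Bin(44, 0.341) + Bin(6, q) ≥ 23]:

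| Share q last seen at target | Expected LOCF rate | Chance of passing |
|---|---|---|
| Missing as not achieved | 30.0% | 1.0% |
| 10% | 31.2% | 1.8% |
| 20% | 32.4% | 3.0% |
| 30% | 33.6% | 4.6% |
| 50% | 36.0% | 9.3% |
| 70% | 38.4% | 16.1% |
| 90% | 40.8% | 25.5% |
| 100% | 42.0% | 31.2% |

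The nominal 2.5% is passed between q = 10% and q = 20%. With 3 dropouts instead of 6, the chance is about 2.5% at q = 30% and 3.7% at q = 50%.

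**Denominator alone.** 21/50 has a lower limit of 28.2% and fails. Without three patients who lack a post-baseline urate, 21/47 has 30.2% and passes. Without two, 21/48 has 29.5% and fails.

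**Other comparators.** With 20 of 44 completers at target, the completer analysis passes (45.5%, lower limit 30.4%). If all 6 stoppers were last seen above 6 mg/dL, LOCF gives 20/50 = 40.0% (26.4%), which fails. If the rate had everyone stayed on drug were 55%, and 10% to 30% of a 12% stopping fraction were last seen at target, LOCF gives 0.88 × 0.55 + 0.12 × 0.10 = 49.6% up to 0.88 × 0.55 + 0.12 × 0.30 = 52.0%, below 55%.

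**The case against.** A reader might infer that LOCF can only inflate the result and that the primary test is therefore anti-conservative in general. The article does not support that. Dosing starts low and is titrated up while urate is above target, so a patient who stops during titration may well be last seen above 6 mg/dL, and LOCF then scores a failure. As shown above, LOCF can fall below the completer rate and below the rate had all stayed on drug. Section 2.3.1 does not say how stoppers are to be counted, so the one-directional statement holds only against missing as not achieved. This part of the objection stands.

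The size also depends on figures that the article does not give. Shares of 50% or more make early stoppers better responders than the 34.1% assumed for completers, and nothing in the text supports that. The lower rows of the table are as admissible as the upper ones. The denominator example is a knife-edge case, and with tests scheduled at week 4 and at discontinuation, three patients without a reading is itself an assumption.

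The study is also labelled exploratory, and a post-baseline reading is a common requirement for an FAS. If the true rate is far above 30%, the rule hardly matters. Section 3 cites 91.3% and 100% at target on 2 and 4 mg/day in an earlier open-label study. A missing-as-failure sensitivity analysis may exist in a plan that is not shown. These arguments lower the severity but do not remove the point: the article states the primary rule itself, and it sets a threshold, a null hypothesis, and "a significance level of α = 0.05 (two-sided) and a power of 1-β 90" percent.

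**Conclusion.** The concern holds in a limited form. The stated LOCF rule and the FAS definition together count patients who stop early at target as week-24 successes, and they remove treated patients without a post-baseline urate. Relative to missing as not achieved among all treated eligible patients, the tested rate can rise but never fall. Relative to completers only, or to continued treatment for all, the direction is open.

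Under the assumptions of 6 dropouts, a true rate of 30% with dropouts as failures, and the exact 23/50 rule, the chance of a false pass moves from 1.0% to between 1.8% and 31.2%. It exceeds the nominal 2.5% once somewhat more than one dropout in ten was last seen at target. The effect matters for the conclusion only when the true rate is near the threshold. Severity: should-fix.

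**What to change.** For the primary outcome, analyse all eligible patients who took at least one dose of dotinurad. Count a week-24 urate that is missing, or that was taken after stopping dotinurad, as not achieved. Keep LOCF in the FAS as a named sensitivity analysis. State this before the data are analysed.

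The change is to wording only. Its price is a lower rate, and lower power, if patients drop out: the step from 44 to 50 replaces dropouts who leave the analysis, but does not compensate for dropouts counted as failures. With exactly 6 dropouts as failures and 23/50 needed, power is about 70% if 55% of completers respond, 97% at 65%, and over 99% at 75%.

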#### 2.3.2 Secondary outcomes

The secondary outcomes of this study will include the following from baseline to observation points at weeks 4, 12, and 24.

Change in serum urate levelsChanges in plasma indoxyl sulfateRenal impairment-related parameters: changes in eGFR, eGFR slope, serum creatinine, and urinary albumin and creatine (urine will be collected at any time and levels corrected for urinary creatine will be used)Changes in doses of the study drug used in the study

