**Figure 1 f1:**
[figure not shown]
Potential mechanisms of action of febuxostat or dotinurad on synthesis and excretion of uric acid and indoxyl sulfate. XOR, xanthine oxidoreductase; URAT1, urate transporter 1; ABCG2, ATP binding cassette, subfamily G, 2; OAT, organic anion transporter; GLUT9, glucose transporter 9.

In this study, indoxyl sulfate will be used as an indicator of effects on ABCG2, OAT1, and OAT3. In patients with impaired renal impairment, the level of indoxyl sulfate in the circulating blood increases, thus a risk factor for CKD progression and cardiovascular complications due to its accumulation in the blood and various organs (11). Thus, lowering plasma indoxyl sulfate concentrations with dotinurad may be associated with a lower risk of cardiovascular disease development and renal disease progression than febuxostat. Therefore, we will also evaluate the eGFR slope before and after dotinurad treatment and its effect on renal function decline. However, further studies are needed for the development of cardiovascular disease, which requires long-term observation periods in large clinical studies.

In a recent prospective, randomized, open-label study comparing the effects of the urate excretion-promoting agent benzbromarone 25 mg/day with febuxostat 20 mg/day in male patients with gout with reduced urinary urate excretion type, the rate of achieving a serum urate target of <6 mg/dL after 12 weeks of treatment was higher in the benzbromarone group than in the febuxostat group (20). Benzbromarone also inhibits urate transport *via* ABCG2, as does febuxostat (12), suggesting that URAT1 inhibitors are more potent in lowering serum urate than XOR inhibitors in hyperuricemia of reduced urate excretion type. Because patients receiving febuxostat will be enrolled in this study, it is not possible to confirm the type of hyperuricemia; however, in general, the majority of patients have a reduced urate excretion type (1). Thus, dotinurad may be more potent than febuxostat in lowering serum urate through its action *via* URAT1 inhibition alone.

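### Last observation carried forward is not limited to the primary outcome: it also fills the continuous secondary outcomes, biasing week-24 changes and, if applied to visit eGFR, flattening the slope

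*Protocol article*

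**What the plan says.** All references are to the protocol article.

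- **Missing data.** Section 2.5 ends with "Missing data in efficacy will be imputed using the last observation carried forward method". It names no outcome and gives no other method. The same paragraph sets out the secondary analyses: "For the secondary outcomes obtained from the metric data, summary statistics will be calculated at each observation point", followed by a one-sample t-test or signed rank test.
- **Outcomes in reach.** Section 2.3.2 lists changes in serum urate and plasma indoxyl sulfate, and "changes in eGFR, eGFR slope, serum creatinine, and urinary albumin and creatine", measured "from baseline to observation points at weeks 4, 12, and 24". Study-drug dose is in the same list ("Changes in doses of the study drug used in the study"). Safety outcomes have their own list (2.3.3) and their own analysis set.
- **Who stays in the analysis.** Under 2.3.4 the full analysis set takes treated, eligible patients who "have serum urate readings at baseline and at least one time point during the observation period". A patient last seen at week 4 is therefore included.
- **Treatment and visits.** Under 2.1 the dose starts at 0.5 mg daily and may be raised stepwise to 4 mg. Table 1 schedules blood and urine tests at weeks 0, 4, 12 and 24 and at discontinuation.
- **Use of the slope.** The Discussion says "we will also evaluate the eGFR slope before and after dotinurad treatment", to judge the effect on renal function decline.

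**The concern.** Carrying a value forward assumes that nothing changes after the last measurement. That suits these outcomes badly, for two reasons.

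First, dose, and so presumably urate, is expected to move during titration. A week-4 value reflects an early dose step, yet it would be reported as a week-24 result. If the patient would have continued and responded further, the change is understated. If the patient stopped the drug and urate rose again, the carried on-drug value overstates it. The rule is therefore not dependably conservative.

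Second, a slope measures change over time, and carried values are flat by construction. The pre-switch slope rests on historical eGFR (2.2.1 requires a value from about 6 months before consent), so filling affects only the post-switch side. Where renal function is falling, a flattened post-switch slope favours the switch. The slope and the indoxyl sulfate change carry the renal and mechanistic interpretation offered in the Discussion.

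**Working it through.** **Plan's own figures.** The article gives no figure for the effect of imputation and no dropout rate. Section 2.4 moves from 44 required to 50 enrolled, which implies 6/50 = 12% lost.

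**Slope for one patient.** Assume a least-squares slope on nominal weeks 0, 4, 12, 24, with missing visits filled first. The mean time is 10, the deviations are −10, −6, 2, 14, and Sxx = 100 + 36 + 4 + 196 = 336. Let true eGFR change by b per week.

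- Last measured at week 4: values 0, 4b, 4b, 4b. Slope = 4b(−6 + 2 + 14)/336 = 40b/336 = 0.119b.
- Last measured at week 12: values 0, 4b, 12b, 12b. Slope = (−24 + 24 + 168)b/336 = 168b/336 = 0.50b.

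**With a discontinuation visit.** Suppose that visit, at week L, supplies the carried value.

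- L between 4 and 12: the fraction kept is (−24 + 16L)/336. For example, L = 8 gives 104/336 = 31%.
- L between 12 and 24: the fraction kept is 14L/336 = L/24. For example, L = 18 gives 75%.

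So 12% and 50% are worst cases for patients who attend that visit.

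**Mean of 50 patients, 6 lost, loss unrelated to slope.**

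- 3 after week 4 and 3 after week 12: (44 + 3×0.119 + 3×0.50)/50 = 45.86/50 = 0.917, a shrinkage of about 8%.
- All 6 after week 12: (44 + 3)/50 = 0.94, or 6%.
- All 6 after week 4: (44 + 0.714)/50 = 0.894, or about 11%.
- Heavier loss of 15 (8 early, 7 late): (35 + 0.952 + 3.5)/50 = 0.789, or 21%.

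**Is the standard error wrong?** Per-patient slopes with a one-sample t interval were simulated: 50 patients, 10,000 runs, units per 24 weeks. The assumptions, which are not in the article, are a mean slope of −2, between-patient SD 3 and visit error SD 3, except where noted.

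| Losses | True mean | Mean after filling | Coverage after filling | Coverage, completers |
|---|---|---|---|---|
| 3 early, 3 late | −2.01 | −1.85 | 94.4% | 94.7% |
| 6 early | −2.00 | −1.78 | 94.2% | 95.1% |
| 6 late | −2.00 | −1.89 | 95.0% | 95.2% |
| 6 early, mean slope −5, SD 2 | −5.00 | −4.46 | 87.9% | 95.1% |
| 3 and 3, leavers decline 4 faster | −2.48 | −1.99 | 89.4% | 90.4% |
| 6 early, leavers decline 4 faster | −2.47 | −1.83 | 84.4% | 90.3% |

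In the first row the reported standard error (0.682) equals the estimator's own sampling SD (0.682). It is about 8% below the completers' 0.740, but it is calibrated. Coverage falls because the mean is biased.

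**Week-24 urate change.** With 3 early and 3 late leavers who would have followed the mean course m on drug, the bias is [3(m4 − m24) + 3(m12 − m24)]/50. Assumed means of −0.5, −1.2 and −1.8 mg/dL (illustrative only) give (3×1.3 + 3×0.6)/50 = 0.11 mg/dL toward zero. If all leave late it is 6×0.6/50 = 0.07; if all leave early, 6×1.3/50 = 0.16.

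**The case against.** The best defence is that this is a small exploratory study, these outcomes are secondary, and the article does not say how the slope is derived. A slope could be computed from whatever eGFR values exist, with no filling, and such detail may sit in a fuller document. That stands as a limit on the slope figures, which are conditional. It does not answer the week-24 changes, because the stated rule reaches them without any further assumption. The discontinuation visit also stands as a mitigation.

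Four stronger readings are tempting, but the article does not support them.

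- **Standard errors are too small.** A reader might infer this because filled values are tested as if observed. It would apply to a pooled regression on filled data, or to one leaver's own slope. It does not follow for the planned one-sample test, as shown above.
- **Dose is imputed after stopping.** Dose is listed as a secondary outcome, but nowhere is it called efficacy data or said to be carried forward.
- **Baseline markers are carried forward as zero change.** The full analysis set requires only a later urate value, so this is possible. However, Table 1 schedules blood and urine tests at the same visits, and no text says that baseline values are carried.
- **An early dip becomes lasting decline.** A patient with a 5-unit dip carried from week 4 scores about −7.8 per year, against +4.7 if recovered by week 12. But +4.7 for a patient with no net change is a least-squares artefact and makes up 4.66/12.42 = 38% of the contrast, so the example overstates what carrying forward does.

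**Conclusion.** The concern holds in limited form. The rule as written is unrestricted and naturally covers the continuous secondary outcomes, for which it is a poor choice. It biases week-24 changes in a direction that depends on the reasons for leaving. For the eGFR slope, the bias is about 8% of the mean (6% to 11%) under four assumptions: visit values are filled before fitting, 6 of 50 are lost, decline is steady, and loss is unrelated to slope. The bias would be smaller where discontinuation visits are attended and larger with heavier loss. It tends to make decline after the switch look milder. The size is modest and the primary responder analysis is not part of this point, but the change is worth making because the rule is stated and easily replaced.

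**What to change.** In section 2.5:

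- Drop last observation carried forward as the main method for continuous outcomes, or keep it only as a sensitivity analysis.
- Analyse change at weeks 4, 12 and 24 from observed values with a repeated-measures mixed model that includes baseline value and visit.
- Estimate eGFR slope from observed eGFR at actual measurement dates, including the discontinuation visit. The visit windows of ±2 and ±4 weeks make actual dates preferable in any case.
- State that neither baseline values nor study-drug dose are carried forward.

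The cost is one paragraph and standard software. The downside is reliance on missing at random. If leavers decline faster for reasons that the observed data do not show, observed-data methods are biased too: completers' coverage also fell to about 90% in that scenario.
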